## Abstract

**Introduction::**

Although it is essential to provide comprehensive rehabilitation after hip fracture to restore the patient to preoperative physical functioning, feasibility issues remain. Here, we describe a protocol for a randomized controlled trial (RCT) to evaluate the effectiveness of fragility fracture integrated rehabilitation management (FIRM) for elderly individuals after hip fracture surgery. We also examine the feasibility of applying FIRM in a chronic-care hospital or community-based setting.

**Methods and analysis::**

Elderly patients will be randomly assigned to either the FIRM, conventional, or control group for a 2-week intervention period following hip fracture surgery. The primary outcome of this study is Koval walking ability. All functional outcomes will be measured 1 and 3 weeks, 3, 6, and 12 months after the surgical intervention. Researchers will be blind to group allocation, and participants will be blind to outcome. A sample size of 282 participants will be necessary to demonstrate the effect of the FIRM program. After the RCT has been conducted in 3 core hospitals, FIRM will be applied in 6 community-based local hospitals to investigate the feasibility of the program. The data will be analyzed using the intention-to-treat principle.

**Trial registration number::**

NCT03430193.

## Introduction

1

### Background

1.1

Although the quality of the surgical and perioperative treatment of hip fracture has improved,^[1]^ the physical and functional recovery after surgery and acute care remains deficient. Before hip fracture, 11% of community-dwelling elderly individuals are bed-ridden and 16% are in long-term-care facilities.^[2]^ Within 1 year after sustaining a hip fracture, individuals experience is a very serious decrease in the quality of their life, and the mortality rate in this group is as high as 36%.^[3]^ A cohort study with the Norwegian Hip Fracture Register (n = 10,325) showed that 58% and 59% of patients had walking problems and pain, respectively, after 12 months of follow up.^[4]^ The high rates of morbidity and mortality after hip fracture have increased the cost of medical care and thus also constitute a serious socioeconomic problem. In Europe, the estimated economic burden imposed by fragility fractures in 2010 was €37 billion, with a 25% increase in the cost expected by 2025.^[5]^ Therefore, it is important to provide multidisciplinary and comprehensive rehabilitation aimed at restoring the patient to preoperative physical functioning after surgery for hip fracture.

Comprehensive rehabilitation after hip fracture usually consists of physical therapy (PT), occupational therapy (OT), fall prevention, nutritional support, psychiatric evaluation, complication care, and discharge planning with environmental modification.^[6]^ In a single-center controlled trial of hip fracture patients 70 years of age or older (n = 1077), comprehensive geriatric care was shown to improve mobility compared with the usual orthopedic care at 4 months.^[7]^ A Taiwanese study compared 3 groups of elderly patients (n = 229) with hip fracture treated with different approaches: usual care, interdisciplinary care (geriatric consultation, continuous rehabilitation, and discharge planning), and comprehensive care (interdisciplinary care plus nutrition consultation, depression management, and fall prevention).^[8]^ This research found a lower risk of depression and malnutrition in the comprehensive care group than in the interdisciplinary care group 1 year after discharge. Therefore, better functional outcomes can be expected following the provision of a comprehensive postoperative rehabilitation program to hip fracture patients.

However, there are several practical problems related to providing comprehensive rehabilitation, such as lack of facilities and human resources, which are directly linked to medical insurance coverage. Although comprehensive treatment can be readily offered at a well-established tertiary care hospital, this is not the case in community-based hospitals. Moreover, the length of hospitalization in a tertiary-care hospital after acute fracture surgery is being reduced,^[9]^ and patients who are discharged early may end up being transferred to a community-based hospital unless their functional recovery is rapid and they can be discharged home. Therefore, we should investigate the feasibility of providing comprehensive rehabilitation to hip fracture patients who are treated in a chronic or community-based setting after surgery and acute in-hospital care.

The Korean Fragility Fracture Rehabilitation Study Group has been involved in establishing a multidisciplinary hip fracture care program consisting of several orthopedic surgeons and a geriatrician. In 2016, it launched a nationwide multicenter project, funded by the Ministry of Health and Welfare, which included a fracture liaison service. The group has since developed a fragility fracture integrated rehabilitation management (FIRM) plan for patients with hip fracture, which it plans to evaluate in a pilot study^[10]^ aimed at investigating the critical rehabilitation pathway for fragility fractures in chronic-care and community-hospital settings.

### Objectives

1.2

We aim to develop a critical pathway for FIRM and compare the effectiveness of this program with those of conventional postoperative rehabilitation and historical control treatment for individuals after hip fracture surgery. We also propose to delineate the feasibility of applying FIRM in a chronic-care or community-based hospital setting.

## Methods

2

### Trial design

2.1

#### Stage 1: Comparison of the effectiveness of FIRM

2.1.1

This study was designed as a participant-blind (to outcome), researcher-blind, multicenter (Seoul National University Bundang Hospital, Chung-Ang University Hospital, and Jeju National University Hospital), randomized controlled trial (RCT) with 3 arms (FIRM, conventional, and historical control groups). During the 2-week postoperative intervention period, patients in the FIRM and conventional groups will participate in the hospital's exercise program beginning 5 to 7 days after hip fracture surgery. Only the intervention group will follow the FIRM program. Functional outcomes will be measure periodically for 12 months after surgery (Fig. 1). The trial has been registered prospectively with the Clinical Trials.gov Registry (NCT03430193) prior to participant recruitment. Important protocol modifications will be communicated to the trial registry.

**Figure 1 F1:**
[figure not shown]
Trial procedure flow diagram.

#### Stage 2: Feasibility of FIRM

2.1.2

After conducting the RCT in 3 core hospitals, the FIRM program will be tested in 6 community-based local hospitals (Chungbuk National University Hospital, Gyeongsang National University Hospital, Kyungpook National University Hospital, Presbyterian Medical Center, Dongguk University Ilsan hospital, and Chonnam National University Bitgoeul Hospital). The aim of this stage is to determine the feasibility and effectiveness of FIRM by applying the same protocol to all participating patients without randomization.

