### Recruitment

2.4

For the comparative clinical trial, all patients will be enrolled in 3 core hospitals. On the second day after hip fracture surgery, patients who meet the inclusion but not the exclusion criteria will be preliminarily screened by researchers in cooperation with orthopedic surgeons. Patients who agree to participate in the study will be finally enrolled. In a test of this protocol, the ratio of patient enrolments among Seoul National University Bundang Hospital, Chung-Ang University Hospital, and Jeju National University Hospital was 5:3:2 compared to the average number of hip fracture surgeries at the 3 hospitals. In stage 2, all participants will be enrolled consecutively.

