### Outcome measures

2.7

The following demographic data will be collected at baseline: age, sex, fracture location and laterality, type of surgery, and underlying disease. Functional outcomes will be measured at 1 (before intervention) and 3 weeks (after 2 weeks’ intervention), 3, 6, and 12 months after operations.

The primary outcome of this study will be Koval walking ability scores^[11]^ (range: 1–7; with a higher score indicating a worse outcome), which rates physical functioning according to walking dependency. The secondary outcomes will be as follows: physical functioning and walking ability, assessed according to the functional ambulatory category^[12]^ (range: 0–5; a lower score indicates a worse outcome) and the modified Rivermead mobility index^[13]^ (range: 0–40; a lower score indicates a worse outcome); balance and fall risk, assessed using the Berg balance scale^[14]^ (range: 0–56; a lower score indicates a worse outcome); cognition, evaluated using the Korean version of the Mini-Mental State Examination^[15]^ (range: 0–30; a lower score indicates a worse outcome); mood, evaluated using the Korean version of the Geriatric Depression Scale^[16]^ (range: 0–30; a lower score indicates a worse outcome); quality of life (QOL), evaluated using the Euro Quality of Life Questionnaire 5-dimensional classification^[17]^ (EQ-5D; range: 0–1; a lower score indicates a worse outcome); ADLs determined using the Korean version of the modified Barthel index^[18]^ (range: 0–100; a lower score indicates a worse outcome) and the Korean version of the Instrumental ADL^[19]^ (range: 0–3; a higher score indicates a worse outcome); and frailty assessed based on fatigue, resistance, ambulation, illnesses, and loss of weight (FRAIL) using the Korean version of the FRAIL scale^[20]^ (K-FRAIL; range: 0–5; a lower score indicates a worse outcome). Functional assessments will be conducted with the control group via telephone surveys performed at the same time points but measures will be limited to the Koval and EQ-5D. The adherence and drop-out rates of the program will be monitored during stage 2, in which FIRM will be applied in the community-based hospital system. Each researcher charged with outcome evaluation at each of the 3 core hospitals will work on standardizing all measuring protocols by arranging a consensus meeting before the start of the study. Regular meetings to discuss ways to unify the measurement methods will then be held.

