### Data analysis

2.8

Data will be collected using a standardized data entry form and entered into the data management system. The intention-to-treat principle will be used for data analysis. Participant characteristics will be described using means and standard deviations for continuous data and frequencies and percentages for categorical data. The 3 groups will be compared using an analysis of variance (ANOVA) or the nonparametric equivalence Kruskal–Wallis test if required. To compare paired data (intragroup) between 2 different points, we will use repeated-measures ANOVA and Friedman tests for continuous and nonparametric data, respectively. Statistical significance will be defined as a *P* value < .05. All statistical analyses will be performed using SPSS version 19.0 for Windows (IBM Corp, Chicago, IL).

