## Discussion

3

Loss of functional independence, which is a long-term sequela of hip fracture,^[23]^ is often accompanied by a deterioration in health-related QOL.^[24]^ Longitudinal studies have shown a decline in the functional status of patients with hip fractures following reductions in rehabilitation services.^[25]^ Conversely, the long-term functional outcomes of patients who received comprehensive rehabilitation in recent clinical trials performed after hip fracture surgery included significantly better mobility and ADL scores.^[7,26,27]^ However, the dissemination of a well-designed rehabilitation program to community-based hospitals is challenging. Our study examines the efficacy of FIRM, a postoperative comprehensive rehabilitation program, and investigates the feasibility of its use in community hospitals with the goal of subsequently implementing it and evaluating its efficacy on a nationwide basis to confirm the findings.

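### Stage 2 is given an effectiveness aim that its single-arm design, with no named comparator, cannot deliver

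*Protocol article*

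**What the plan says.** Section 2.1.2 states that Stage 2 will "determine the feasibility and effectiveness of FIRM by applying the same protocol to all participating patients without randomization". Section 2.4 (Recruitment) adds: "In stage 2, all participants will be enrolled consecutively". The only measures specific to this stage are in section 2.7 (Outcome measures): "The adherence and drop-out rates of the program will be monitored during stage 2".

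Elsewhere the community stage is described as feasibility. The heading of section 2.1.2 names feasibility alone. The Abstract says "FIRM will be applied in 6 community-based local hospitals to investigate the feasibility of the program", and section 1.2 (Objectives) says "We also propose to delineate the feasibility of applying FIRM in a chronic-care or community-based hospital setting".

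Section 2.8 (Data analysis) describes a comparison of the three groups and a within-group comparison: "To compare paired data (intragroup) between 2 different points, we will use repeated-measures ANOVA and Friedman tests". It assigns neither to Stage 2.

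**The concern.** An effectiveness statement needs a reference: what would have happened to these patients without the programme. Stage 2 has none. Functional assessment starts 1 week after surgery, so any change seen later mixes the effect of FIRM with whatever course the patients would have followed anyway.

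The protocol recognises this in Stage 1. Section 2.6.3 includes a group discharged without physical therapy in order to show the natural course. Stage 2 drops that reference and keeps the effectiveness aim.

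At stake is what may be concluded from Stage 2. With the aim as worded, a functional improvement in the six hospitals could be reported as evidence that FIRM works there, when the design cannot show it. Readers also cannot tell which aim the Stage 2 results will be held to.

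**Working it through.** **1. Is there a comparator?** The places that describe Stage 2, set side by side:

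| Place | What it gives for Stage 2 |
|---|---|
| 2.1.2, heading | feasibility |
| 2.1.2, aim | feasibility and effectiveness; all patients treated alike; no randomization |
| Abstract | feasibility |
| 1.2 Objectives | feasibility |
| 2.4 Recruitment | consecutive enrolment |
| 2.7 Outcome measures | adherence and drop-out |
| 2.8 Data analysis | nothing specific to Stage 2 |

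No comparator, target or benchmark appears in any of them. Effectiveness appears in the aim sentence alone.

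**2. Which planned analysis could serve the aim?** The three-group comparison in 2.8 needs three groups. Of the comparisons described there, only the within-group one can be run on a single arm. This is reached by elimination; the document does not say so.

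**3. What would a within-group test show if FIRM did nothing?** The plan states no Stage 2 figure, so there is none to reproduce. The following is an illustration.

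Inputs:
- SD = 1.075 Koval grades, from section 2.3. Taking it as the SD of within-patient change is an assumption; the section does not say so.
- Two-sided alpha 0.05, matching the significance level in 2.8.
- Stage 2 sample size n: not given. Assumed 30, 60 and 94 (94 is the Stage 1 recruitment target per group).
- Natural recovery r, as the size of improvement in grades: not given. Assumed 0.25 and 0.5.
- True FIRM effect: zero.

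Formulas: SE = 1.075/√n; noncentrality λ = r/SE; probability of significant improvement = P(T > c), where T is noncentral t with n − 1 degrees of freedom and noncentrality λ, and c is the 97.5% point of the central t with the same degrees of freedom.

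| r | n | SE | λ | c | Probability |
|---|---|---|---|---|---|
| 0.25 | 30 | 0.196 | 1.27 | 2.045 | 23% |
| 0.25 | 60 | 0.139 | 1.80 | 2.001 | 43% |
| 0.25 | 94 | 0.111 | 2.25 | 1.986 | 61% |
| 0.5 | 30 | 0.196 | 2.55 | 2.045 | 69% |
| 0.5 | 60 | 0.139 | 3.60 | 2.001 | 94% |
| 0.5 | 94 | 0.111 | 4.51 | 1.986 | 99% |

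If the whole pilot difference of 1.034 in section 2.3 were natural recovery, the probability would exceed 99% at all three sizes. Section 2.3 does not say whether 1.034 is a within-patient change or a between-group difference, so that case is only an upper end.

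Even the mildest row lies well above the 2.5% chance of a significant improvement that this test has when there is no change at all.

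**The case against.** The strongest defence is that this is one loose word in one sentence. Most of the article frames Stage 2 as feasibility, the effectiveness question belongs to the randomized Stage 1, and the only measures specific to Stage 2 are feasibility measures. In that context effectiveness might mean no more than observing outcomes under community delivery. An article also leaves detailed Stage 2 analysis to the full protocol or analysis plan. Eligibility and protocol are shared between stages, so a comparison with Stage 1 is not ruled out.

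Part of this stands: it limits the weight of the point and shows how cheap the repair is. It does not rescue the aim. The sentence says effectiveness will be determined by treating everyone, and no later analysis detail makes that possible without a comparator. A comparison with Stage 1 arms is not mentioned, and it would be non-randomized across different hospitals and periods.

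Four stronger readings are tempting and are not supported:

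- *The plan commits to a before-after significance test for Stage 2.* Section 2.8 ties no test to Stage 2, and its within-group sentence serves the Stage 1 arms equally well.
- *A significant result is almost certain.* That depends on the sample size, the SD of change and the natural recovery, none of which is given for Stage 2. Nor does the document say that patients improve under any care; section 2.6.3 gives the natural course no direction.
- *The Discussion contradicts the Stage 2 aim by deferring efficacy.* Its words are "investigates the feasibility of its use in community hospitals with the goal of subsequently implementing it and evaluating its efficacy on a nationwide basis". This concerns a later nationwide evaluation and does not exclude effectiveness from the six-hospital stage.
- *A Stage 2 result would by itself justify roll-out.* No section says this. Stage 1 comes first, and further evaluation is foreseen.

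**Conclusion.** The point holds as a mismatch between aim and design: section 2.1.2 promises to determine effectiveness from a consecutive single arm with no named comparator. It is something the document states wrongly, and does not depend on detail left to another document. The conclusion rests on the wording alone and needs no calculation.

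The consequence is less certain. If Stage 2 were judged by a paired test while FIRM added nothing, the chance of significant improvement would run from 23% to 99% over the assumed 0.25 to 0.5 grade of recovery and 30 to 94 patients. Whether or not such a test was significant, it would not measure effectiveness.

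The weight is moderate. Stage 1 allocation, sample size and primary analysis are unaffected, but what Stage 2 may conclude is affected. The change should be made before Stage 2 results are reported.

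**What to change.** In section 2.1.2, delete *and effectiveness* from the Stage 2 aim, so that it agrees with its heading, the Abstract and the Objectives. Keep adherence and drop-out, already planned in section 2.7, as the Stage 2 endpoints. Report Stage 2 functional change descriptively with confidence intervals, and state that no effectiveness conclusion will be drawn from within-group tests.

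If the sponsor wants to keep an effectiveness aim, the protocol must instead name the comparator and say how confounding between hospitals and periods will be handled.

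The cost of the main fix is a wording change and a descriptive table. The downside is that the sponsor gives up an effectiveness claim for Stage 2, which this design cannot support.

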### Participants and eligibility criteria

2.2

Elderly patients (≥65 years old) who have undergone surgery for femoral neck, intertrochanteric, or subtrochanteric fracture, regardless of surgery type (internal fixation, bipolar hemiarthroplasty, or total hip arthroplasty) will be included. Patients who have experienced the following will be excluded: hip surgery for infection, arthritis, implant loosening, or avascular necrosis; femoral shaft fracture, acetabular fracture, isolated fracture of the greater or lesser tuberosity, or periprosthetic fracture; pathologic fracture; combined multiple fracture; revision surgery; and severe cognitive dysfunction (obey command ≤ 1 step); patients who refuse to participate in a clinical trial will also be excluded. The eligibility criteria will be applied at stages 1 and 2.

### Sample size

2.3

According to the preliminary and unpublished data of a pilot study, the mean difference and standard deviation of Koval walking ability (as a primary outcome) were 1.034 and 1.075, respectively. To detect a mean difference in the Koval walking ability grade of 0.5 for the FIRM group (0 for the conventional group and −0.5 for the control group) with at least 80% power and a significance level of 0.05 using a 2-tailed test, each group must include 85 patients (255 in total). To allow for 10% attrition, our aim is to recruit 94 patients per group (282 in total). PASS version 14.0 (NCSS, Kaysville, UT) was used to calculate the required sample size.

### Recruitment

2.4

For the comparative clinical trial, all patients will be enrolled in 3 core hospitals. On the second day after hip fracture surgery, patients who meet the inclusion but not the exclusion criteria will be preliminarily screened by researchers in cooperation with orthopedic surgeons. Patients who agree to participate in the study will be finally enrolled. In a test of this protocol, the ratio of patient enrolments among Seoul National University Bundang Hospital, Chung-Ang University Hospital, and Jeju National University Hospital was 5:3:2 compared to the average number of hip fracture surgeries at the 3 hospitals. In stage 2, all participants will be enrolled consecutively.

### Randomization and blinding procedure

2.5

Participants will be randomly assigned to 1 of the 3 groups using a computerized random number generator. The principal researcher will be blind to group allocation. Blinding will be initiated by a research associate implementing the randomization process described above. The associate researchers in the 3 hospitals will notify each participant's therapist of group allocation, enabling the therapist to implement the assigned rehabilitation protocol while maintaining the blinding of the other researchers. The principal researcher and the statistician will continue to be blind to group allocation, with the nominal group names assigned by the research associate maintained throughout data analysis. Outcome variables will be measured by researchers who are not involved in patient allocation. It is impossible to blind either the therapists conducting the interventions or the participants to group allocation. Nonetheless, only after their participation in the study is over will the patients be notified of the results and outcome measures.

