#### Control group

2.6.3

This group will consist of an age- and sex-matched historically controlled cohort. Participants will be discharged without having received PT during the postoperative hospitalization period. The aim will be to determine the natural course of the patients’ functional status.

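### The control group is described both as randomly assigned and as a historical matched cohort; if it is historical, one third of the planned sample is not randomised

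*Protocol article*

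**What the plan says.** **Statements that the control is randomised**

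- The methods paragraph of the abstract reads: "Elderly patients will be randomly assigned to either the FIRM, conventional, or control group for a 2-week intervention period following hip fracture surgery".
- Section 2.5: "Participants will be randomly assigned to 1 of the 3 groups using a computerized random number generator".

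**Statements that the control is historical**

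- Section 1.2 compares FIRM with "conventional postoperative rehabilitation and historical control treatment".
- Section 2.6.3: "This group will consist of an age- and sex-matched historically controlled cohort".

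**Both at once**

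- Section 2.1.1 calls the study a "randomized controlled trial (RCT) with 3 arms (FIRM, conventional, and historical control groups").

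**Statements that read as prospective**

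- Section 2.3 counts the control among the groups to be recruited, at 94 each (282 in total).
- Section 2.4 has every patient of the comparative trial enrolled at the three core hospitals, with screening on the second day after surgery.
- Section 2.6.3, straight after defining the historical cohort: "Participants will be discharged without having received PT during the postoperative hospitalization period".
- Section 2.7: "Functional assessments will be conducted with the control group via telephone surveys performed at the same time points", limited to Koval and EQ-5D.

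**Analysis**

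- Section 2.8 applies intention-to-treat without restriction and states: "The 3 groups will be compared using an analysis of variance (ANOVA"), or by Kruskal–Wallis.

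**The concern.** Random allocation and membership of a past cohort exclude each other. Matching on age and sex is a way of selecting a comparison group that was not randomised; a randomised arm does not need it. This goes beyond a slip in a label, because the conflict carries through to the recruitment target, the enrolment procedure, the follow-up schedule and the analysis set.

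What is at stake is how a difference against control may be read. If the cohort is historical, only FIRM versus conventional is protected by randomisation. The cohort is matched on age and sex alone and defined by having had no PT. It could differ from the randomised patients in fracture location, type of surgery, underlying disease, early walking level and period of care. It is also assessed by telephone. Followed as written, the plan would report a difference against this cohort as a randomised, intention-to-treat result. The cohort would also enter the global 3-group test, so that test could be significant even if FIRM and conventional did not differ.

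**Working it through.** **1. Can the statements be reconciled?**

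| Section | Control is randomised | Control is historical | Wording is prospective |
|---|---|---|---|
| Abstract | yes | | |
| 1.2 | | yes | |
| 2.1.1 | yes (3-arm RCT) | yes | |
| 2.3 | | | yes (94 to recruit) |
| 2.4 | | | yes (all enrolled on site) |
| 2.5 | yes | | |
| 2.6.3 | | yes, by definition | yes (future tense) |
| 2.7 | | | yes (same time points) |

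No reading satisfies all the rows. If the control is historical, the abstract and 2.5 are wrong, and 2.3 and 2.4 do not describe it. Surveys from week 1 to month 12 would be possible only if those data already exist. If the control is prospective and randomised, 1.2, 2.1.1 and 2.6.3 are wrong.

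**2. The plan's own sample size (section 2.3)**

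Inputs: difference 0.5, SD 1.075, two-sided alpha 0.05, power at least 80%.

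- Plain two-sample formula: n = 2 × (1.075/0.5)² × (1.960 + 0.842)² = 72.6, so 73 per group (74 by t-test).
- The stated 85 is matched by dividing by 0.864, the minimum relative efficiency of the Mann–Whitney test: 73/0.864 = 84.5, so 85. The article does not name this step.
- 85 × 1.1 = 93.5, so 94. Totals: 3 × 85 = 255 and 3 × 94 = 282, as stated.

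The point does not depend on how 85 was obtained.

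**3. Share affected if the control is historical**

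- Not randomised: 94/282 = 85/255 = 33.3%.
- Randomised: 2 × 94 = 188 recruited, 2 × 85 = 170 evaluable.

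**4. What remains for FIRM versus conventional**

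SE = 1.075 × √(2/85) = 0.165, and 0.5/0.165 = 3.03. Power is 85.4% (t-test) or 85.8% (normal approximation), above the 80% target at an unadjusted 5% level.

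**5. Illustration of an unprotected comparison**

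The shift sizes are assumptions, because the article gives no estimate of bias. Suppose treatment has no effect and only the control cohort differs, for non-causal reasons, by b Koval grades. The t-test (168 df) has non-centrality b/0.165. The 3-group F-test (2 and 252 df) has non-centrality 85 × (2/3) × b²/1.075².

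| Assumed shift b | Control vs one randomised arm, P<.05 | 3-group ANOVA, P<.05 |
|---|---|---|
| 0 | 5% | 5% |
| 0.1 | 9% | 9% |
| 0.2 | 23% | 22% |
| 0.3 | 44% | 45% |
| 0.5 | 85% | 89% |

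For scale, 0.5 is the whole step that section 2.3 assumes between conventional and control.

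**The case against.** **The historical reading is not established.** A reader might infer that one third of the sample is certainly not randomised and that the RCT claim is false. The article does not settle this. Sections 2.3 and 2.4 recruit and enrol, 2.6.3 uses the future tense and 2.7 surveys controls at the common time points. All of that fits a prospective group. This stands, so the one-third figure is conditional. It does not remove the contradiction, since one set of sections must be wrong either way.

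**No confounding is shown.** A reader might also infer that the control comparison is biased. The article gives no data on the cohort, and the error rates above follow entirely from assumed shifts. This also stands: what can be said is that the comparison would lack the protection of randomisation.

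**Adjustment may be planned elsewhere.** Section 2.8 is a condensed paragraph, and covariate adjustment may sit in an analysis plan that is not shown. Its absence is therefore not part of this point. But no analysis plan can turn a past cohort into a randomised arm.

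**The article is open about the control.** Sections 1.2 and 2.1.1 use the word historical, and 2.6.3 gives the aim as describing the natural course. This softens the risk of misreading only in part, because 1.2 also makes the control a comparator for effectiveness and 2.8 tests it together with the other groups.

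**Conclusion.** The contradiction is certain and lies in the current text, so it must be corrected before results are reported. If the control is historical, as its only explicit definition says, then 94 of 282 patients (33%) are not randomised. The 3-arm RCT label, the unrestricted intention-to-treat statement and the pooled 3-group test do not then hold for that group. A modest non-causal shift would be enough to produce frequent false-positive findings against control: 23% at 0.2 grade and 44% at 0.3, under the assumed shifts and the planning SD. Whether any such shift exists is unknown. FIRM versus conventional keeps its randomisation under either reading.

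**What to change.** **First, state which description applies** and correct the abstract and sections 1.2, 2.1.1, 2.3, 2.4, 2.5, 2.6.3, 2.7 and 2.8 to match. If the control is prospective and randomised, the historical and matched-cohort wording has to go.

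**If the control is historical:**

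- Describe a two-arm randomised trial of FIRM versus conventional (94 each, 188 randomised), plus a non-randomised external cohort of up to 94.
- Limit the RCT and intention-to-treat statements and the primary conclusion to FIRM versus conventional, and take the control out of the pooled 3-group test.
- Report the control comparison separately, as supportive and observational. Adjust for age, sex, fracture location, type of surgery, underlying disease and early Koval score, each only where it was actually recorded for the cohort. Section 2.7 specifies only telephone Koval and EQ-5D as functional measures for controls, and a past cohort may have no 1-week value.
- Use only time points at which the cohort was actually assessed, and name telephone assessment as a limitation that covariate adjustment does not remove.

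**Cost:** changes of wording and one separate analysis, with no additional randomised patients. How far adjustment is possible depends on what the cohort's records contain. The downside is that the contrast with no PT loses its randomised label.
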